### **3.2.3.3 Allocation**

Eighty (80) patients meeting the eligibility requirements will be randomized on a 1:1 basis to one of the two treatment groups:

1. Group A: will receive Raltegravir + Ritonavir-boosted Darunavir
2. Group B: will receive Tenofovir + Emtricitabine + Ritonavir-boosted Darunavir

Patients will be provided with medications according to their treatment groups and will be instructed to take them as previously described. The patients will also be instructed on the procedure for reporting of adverse experiences.

### **3.2.3.4 Treatment/Evaluation/Follow-up**

The investigator will follow the patients according to standard of care.

Laboratory assessments (including HIV RNA and CD4 Cell Count) will be performed locally at the Screen and at all time-points indicated in the study Flow Chart.

#### **Measurement of serum free insulin.**

Serum free insulin levels will be measured by radioimmunoassay, using a double antibody technique (Coat-A-Count; Diagnostic Products Corp., Los Angeles, CA). Results will be reported at  $\mu\text{U/ml}$ . Insulin resistance will be evaluated by calculation of the homeostasis model assessment (HOMA-IR) calculated from fasting plasma glucose (FPG) and serum free insulin (SFI) with the formula  $\text{HOMA-IR} = \text{SFI in mU/l} \times \text{FPG in mg/dl} / 405$ .

**In Vivo Lipoprotein Analysis.**

***Lipoprotein subtype analysis.*** At baseline and every 16 weeks 2 serum aliquots each with a fill volume of 1 mL will be drawn from the patient after a 12 hours fast per standard blood draw procedures. These samples will be coded with no patient identifiers and frozen and shipped to Pacific Biometrics, Inc. (Seattle, WA) on dry ice. Only the investigators at the VA North Texas Health Care system will be able to link the coded samples to the patient enrolled.

LDL subtypes (LDL1, LDL2a, LDL2b, LDL3, LDL4, LDL5, LDL6, LDL7) and HDL subtypes will be measured using polyacrylamide gradient gel electrophoresis (Berkeley HeartLab, Inc.). Apolipoproteins A-I, A-II, B, C-I, C-II and E will be measured by Immunoturbidimetric assay.

***DEXA Scans.*** Whole body DEXA (Dual Energy X-ray Absorptiometry) scans with 3 bony sites will be done at the VA North Texas Health Care System at baseline and at week 48 of therapy to assess any changes in percent body fat, lean body mass, and bone density.

At each visit, assessment of serious adverse experiences and drug related adverse experiences that result in Grade 3 or above laboratory toxicity, lead to treatment interruption, or discontinuation, and pregnancy test for women of childbearing potential must be performed. Additional recommended procedures are listed on the study flow chart (Section 1.6).

At each visit, the investigator/study coordinator will ascertain the patient's drug compliance, tolerance to the drugs and clinical response prior to providing additional drug supply to last until the next clinic visit. Empty bottles must be returned by the patient to the investigator and recorded in the drug accountability log at the site. All unused study medication and empty bottles will be returned to the Principal Investigator.

All patients that discontinue from the study early must return to the clinic during the follow-up prior for completion of safety assessment and pregnancy test for women of childbearing potential. Additional recommended procedures are listed on the study flow chart.

**3.2.3.5 Discontinuation/Withdrawal from Study**

Any patient who becomes pregnant during the course of the study must immediately be discontinued from the study. All pregnancies must be reported immediately to the Principal Investigator and must be followed to the completion/termination of the pregnancy. The outcome of the pregnancies must be reported to the Principal Investigator.

Patients may discontinue study therapy:

1. If medically appropriate due to potential clinical and/or laboratory adverse experiences. Discontinuation from the study due to an adverse experience is considered a study-specific adverse event and must be recorded on the appropriate case report form.

**IRB Approved**

**06/24/13**

[figure not shown]

2. If the patient or investigator believes it to be in the patient's best interest to discontinue.

All patients who discontinue from the study must be reported promptly to one of the Principal Investigator. As soon as possible after discontinuation of all study therapy, patients will have withdrawal visit as noted in the study flow chart.

Study/patients may withdraw at any time or be dropped from the study at the discretion of the investigator should any untoward effects occur. In addition, a subject/patient may be withdrawn by the investigator if he/she violates the study plan or for administrative and/or other safety reasons. The investigator or study coordinator must notify the Primary Investigator immediately when a subject/patient has been discontinued/withdrawn due to an adverse experience (telephone or FAX). When a subject/patient discontinues/withdraws prior to study completion, all applicable activities scheduled for the final study visit should be performed at the time of discontinuation. Any adverse experiences which are present at the time of discontinuation/withdrawal should be followed in accordance with the safety requirements outlined in section 3.3 SAFETY MEASUREMENTS –

### **3.3 Safety Measurements**

#### **3.3.1 Clinical and Laboratory Measurements for Safety**

Safety data of serious adverse experiences and drug-related adverse experiences that result in Grade 3 or above laboratory toxicity, lead to treatment interruption, or discontinuation will be collected at each visit. It is recommended that the patient be followed for laboratory safety assessment according to the standard of care. Note that laboratory assays are to be evaluated by the investigator's local laboratory. The laboratory safety assessments should include a chemistry evaluation with serum creatinine, liver function tests, and a CBC. Additional laboratory assessments should be performed per standard of care at the investigator's discretion.

In case of grade 3 or 4 laboratory abnormalities, it is recommended to retest within 48 hours for confirmation.

#### **3.3.2 Definition and Classification of Adverse Events**

##### **3.3.2.1 Adverse Event**

An adverse event is any untoward medical occurrence in a clinical study subject administered a pharmaceutical product. An adverse event does not necessarily have a causal relationship with the treatment. An adverse event can therefore be any unfavorable and unintended sign (including an abnormal finding), symptom, or disease temporally associated with the use of a medicinal (investigational) product, whether or not related to the medicinal (investigational) product. (Definition per International Conference on Harmonisation [ICH])

This includes any occurrence that is new in onset or aggravated in severity or frequency from the baseline condition, or abnormal results of diagnostic procedures, including

**IRB Approved**

**06/24/13**

[figure not shown]

laboratory test abnormalities.

Note: Adverse events can occur from the signing of the informed consent onwards.

### 3.3.2.2 Serious Adverse Event

A serious adverse event as defined by ICH is any untoward medical occurrence that at any dose meets any of the following conditions:

- results in death
- is life-threatening  
(The subject was at risk of death at the time of the event. It does not refer to an event that hypothetically might have caused death if it were more severe.)
- requires inpatient hospitalization or prolongation of existing hospitalization
- results in persistent or significant disability/incapacity, or
- is a congenital anomaly/birth defect

**Note:** Medical and scientific judgment should be exercised in deciding whether expedited reporting is also appropriate in situations other than those listed above. For example, important medical events may not be immediately life threatening or result in death or hospitalization but may jeopardize the subject or may require intervention to prevent one of the outcomes listed in the definition above. Any adverse event is considered a serious adverse event if it is associated with clinical signs or symptoms judged by the investigator to have a significant clinical impact.

- **Unlisted (Unexpected) Adverse Event**

An unlisted adverse event, the nature or severity of which is not consistent with the applicable product information. For an investigational product, the expectedness of an adverse event will be determined by whether or not it is listed in the Investigator's Brochure. For a comparator product with a marketing authorization, the expectedness of an adverse event will be determined by whether or not it is listed in the Summary of Product Characteristics (SmPC).

- **Associated With the Use of the Drug**

An adverse event is considered associated with the use of the drug if the attribution is possible, probable, or very likely by the definitions listed below.

### 3.3.2.3 Attribution Definitions

- **Not related**  
An adverse event that is not related to the use of the drug.
- **Doubtful**  
An adverse event for which an alternative explanation is more likely, e.g., concomitant drug(s), concomitant disease(s), or the relationship in time suggests that a causal relationship is unlikely.

**IRB Approved**

**06/24/13**

[figure not shown]

- **Possible**

An adverse event that might be due to the use of the drug. An alternative explanation, e.g., concomitant drug(s), concomitant disease(s), is inconclusive. The relationship in time is reasonable; therefore, the causal relationship cannot be excluded.

- **Probable**

An adverse event that might be due to the use of the drug. The relationship in time is suggestive (e.g., confirmed by dechallenge). An alternative explanation is less likely, e.g., concomitant drug(s), concomitant disease(s).

- **Very likely**

An adverse event that is listed as a possible adverse reaction and cannot be reasonably explained by an alternative explanation, e.g., concomitant drug(s), concomitant disease(s). The relationship in time is very suggestive (e.g., it is confirmed by dechallenge and rechallenge).

### 3.3.3 Recording and Reporting of Adverse Experiences

#### 3.3.3.1 All Adverse Events

All adverse events will be documented from the time a signed and dated informed consent form is obtained until completion of the last study-related procedure. Those meeting the definition of serious adverse events must be reported using the Serious Adverse Event Form, including serious adverse events reported to the investigator within 30 days after the subject has completed the last dose of study drug.

All adverse events, regardless of seriousness, severity, or presumed relationship to study therapy, must be documented using medical terminology in the source documents. Whenever possible, diagnoses should be given when signs and symptoms are due to a common etiology (e.g., cough, runny nose, sneezing, sore throat, and head congestion should be reported as "upper respiratory infection"). Investigators must also document their opinion concerning the relationship of the adverse event to study therapy. All measures required for adverse event management must be recorded in the source document.

#### 3.3.3.2 Serious Adverse Events

All serious adverse events occurring during clinical studies will be reported to the appropriate Merck and Tibotec Therapeutics Clinical Affairs contact persons by investigational staff within 24 hours of their knowledge of the event.

Information regarding serious adverse events will be reported to the Institutional Review Board and transmitted to Tibotec Therapeutics Clinical Affairs using the Serious Adverse Event Form, which must be signed by the Primary Investigator. The initial report of a serious adverse event may be made by facsimile (fax to Merck and to Tibotec Therapeutics Clinical Affairs [contact]).

**IRB Approved**

**06/24/13**

[figure not shown]

All serious adverse events that have not resolved by the end of the study, or that have not resolved upon discontinuation of the subject's participation in the study, must be followed until any of the following occurs:

- the event resolves
- the event stabilizes
- the event returns to baseline, if a baseline value is available
- the event can be attributed to agents other than the study drug or to factors unrelated to study conduct
- when it becomes unlikely that any additional information can be obtained (subject or health care practitioner refusal to provide additional information, lost to follow-up after demonstration of due diligence with follow-up efforts)

The cause of death of a subject in a clinical study, whether or not the event is expected or associated with the investigational agent, is considered a serious adverse event. Any event requiring hospitalization (or prolongation of hospitalization) that occurs during the course of a subject's participation in a clinical study must be reported as a serious adverse event, except hospitalizations for:

- social reasons in absence of an adverse event
- surgery or procedure planned before entry into the study

### 3.3.3.3 Pregnancies

Subject pregnancy must be reported by the investigational staff within 1 working day of their knowledge of the event using the Pregnancy Report form. Any subject who becomes pregnant during the study must be promptly withdrawn from the study. Follow-up information regarding the outcome of the pregnancy and any postnatal sequelae in the infant will be required.

Because the study drug may have an effect on sperm, pregnancies in partners of male subjects included in the study will be reported by the investigational staff within 1 working day of their knowledge of the event using the Pregnancy Report form.

## 3.4 Data Analysis

The primary analysis of efficacy and safety will be based upon the All Patients As Treated (APaT) approach which includes all patients who received one or more doses of the test drug therapy.

The primary endpoint is the comparison of the efficacy of the test regimen (Raltegravir + Darunavir) to Tenofovir + Emtricitabine + Darunavir. The mean effects of the test regimen (Raltegravir + Darunavir) will be compared to comparator regimen.

The analysis will be time to loss of virologic response (TLOVR) [12]. This analysis defines responders as subjects maintaining a minimum of two sequential HIV viral load <50 c/mL through the scheduled visits without intervening replicated rebounds or treatment discontinuations.

**IRB Approved**

**06/24/13**

[figure not shown]

Logistic regression analysis will be used to analyze outcome data to determine the difference between the two regimens. With 40 patients enrolled in each arm, the study has 80% power to rule out a 15% difference in efficacy between the two regimens. This assumes a true response rate of 85% for both treatment groups.

The reasons for failure at week 48 should be the primary reason for the earliest treatment failure. For any visit, subjects who have achieved confirmed virologic success (two consecutive visits with HIV viral load < 50 copies/mL) will be considered successes. All others should be classified into the other appropriate categories listed in Table 2. All events occurring in the window should be considered events for that visit.

All patients who take study medication will be included in the analysis of safety and tolerability. Only those adverse experiences that occur while on study therapy, or within 14 days after discontinuation of study therapy will be included in the analysis.

For assessment of safety and tolerability, counts and percentages of patients with clinical or laboratory adverse experiences of the following type will be tabulated (1) serious adverse experience, (2) drug-related adverse experiences that result in grade 3 or above laboratory toxicity; (3) drug related adverse experiences that lead to treatment interruption; (4) drug related adverse experiences leading to discontinuation.

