**Table 2. Display of 48-week efficacy outcome as calculated using the FDA suggested algorithm [12]**

| Outcome at 48 weeks                                                                                              | Raltegravir +
Darunavir
N (%) | Tenofovir +
Emtricitabine +
Darunavir
N (%) |
|-------------------------------------------------------------------------------------------------------------------------|----------------------------------------------|----------------------------------------------------------------|
| VL <50                                                                                                        | xx (xx%)                                     | xx (xx%)                                                       |
| VL > 50 (Confirmed)
Rebound
Never suppressed through week 48
Drug change due to virologic failure | xx (xx%)                                     | xx (xx%)                                                       |
| Death                                                                                                            | xx (xx%)                                     | xx (xx%)                                                       |
| Drug change or discontinuation due to
adverse events                                                         | xx (xx%)                                     | xx (xx%)                                                       |
| Drug change or discontinuation due to
other reasons                                                          | xx (xx%)                                     | xx (xx%)                                                       |
| Consent withdrawn                                                                                                | xx (xx%)                                     | xx (xx%)                                                       |
| Loss to follow-up                                                                                                | xx (xx%)                                     | xx (xx%)                                                       |
| Nonadherence                                                                                                     | xx (xx%)                                     | xx (xx%)                                                       |

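### The visit-level success rule in section 3.4 omits the maintenance condition, so it contradicts the protocol's own responder definition and the failure rows of Table 2

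*Protocol*

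**What the plan says.** Section 3.4 of the Protocol describes response in two places.

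- **Responder definition** (section 3.4, and in nearly the same words in section 2.6). After at least two successive values below 50, suppression must hold "through the scheduled visits without intervening replicated rebounds or treatment discontinuations".
- **Visit-level rule** (later in section 3.4, in the paragraph that leads to Table 2). "For any visit, subjects who have achieved confirmed virologic success (two consecutive visits with HIV viral load < 50 copies/mL) will be considered successes". The next sentence deals with everyone else: "All others should be classified into the other appropriate categories listed in Table 2".

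The sentence just before the visit-level rule covers attribution: "The reasons for failure at week 48 should be the primary reason for the earliest treatment failure".

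Table 2 divides confirmed values above 50 into rebound, "Never suppressed through week 48", and drug change for virologic failure. It has separate rows for death, for drug change or discontinuation (adverse events, other reasons) and for loss to follow-up, among others. Its title cites the same FDA guidance (reference 12) as the responder definition.

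**The concern.** The visit-level rule assigns success first, on the strength of having reached two consecutive values below 50. Only subjects left over can enter a failure row. Nothing in the rule takes success away after a rebound, a discontinuation, a change of regimen, a death or a loss to follow-up.

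The responder definition a few lines earlier does take it away. Two analysts working from the same section could therefore report different responder counts. The count from the visit-level rule can only be equal or higher. The primary objective (section 2.1.2) is to show comparable virologic efficacy, so a rule that turns late failures into successes can hide a real difference between the arms.

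**Working it through.** **Step 1: apply both rules to the same histories.** After baseline, viral load is measured at weeks 2, 4, 8, 16, 24, 32, 40 and 48 (sections 1.6 and 2.4.2). The table gives status at week 48. The middle column is a more lenient reading, in which the two visits must be the current one and the one before it.

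| History | Visit rule as written | Visit rule, current and previous visit | Responder definition |
|---|---|---|---|
| Below 50 from week 8 to week 48 | success | success | success |
| Below 50 at weeks 8, 16, 24; 50 or above from week 32 | success | failure | failure |
| Below 50 at weeks 8, 16; drug stopped at week 20, no later values | success | failure | failure |
| Below 50 at weeks 8, 16; 50 or above at weeks 24, 32; below 50 at weeks 40, 48 | success | success | failure |
| Never below 50 | failure | failure | failure |

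As written, the rule disagrees with the definition on the three middle histories. The lenient reading removes two of these disagreements but not the third: a subject re-suppressed after a replicated rebound still counts as a success, although the definition excludes that subject. Neither reading of the sentence matches the definition.

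**Step 2: check against Table 2.** A rebound requires earlier suppression. If everyone with confirmed earlier suppression is already a success, nobody is left for the rebound row. The rule cannot be applied literally to the table it is meant to fill.

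**Step 3: size.** The protocol gives no figure for this classification, so there is none to reproduce. Inputs from section 3.4 are 40 subjects per arm, an assumed true response p = 85% and a difference of 15 points to be ruled out. Let f be the share of failures that occur after two consecutive values below 50. The documents do not give f, so it is varied from 0 to 1.

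Response under the visit rule = p + (1 − p) × f.

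Gap between arms with the same f in both = 15 × (1 − f) points, taking true responses of 85% and 85 − 15 = 70%.

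| f (assumed) | True 85% is tabulated as | True 70% is tabulated as | Tabulated gap (true gap 15) |
|---|---|---|---|
| 0 | 85% | 70% | 15 |
| 0.25 | 0.85 + 0.15 × 0.25 = 88.75% | 77.5% | 11.25 |
| 0.50 | 92.5% | 85% | 7.5 |
| 0.75 | 96.25% | 92.5% | 3.75 |
| 1 | 100% | 100% | 0 |

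In patients: 40 × 0.15 = 6 true failures per arm. If 2 to 4 of them follow suppression, the table shows 36 to 38 of 40, or 90% to 95%. If f differs between arms, the tabulated gap may shrink, vanish or grow.

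**The case against.** The best defence is context. The responder definition is given twice, once just before the visit-level rule. Table 2 names rebound and discontinuation as failures, and its title cites the same guidance as the definition. The preceding sentence attributes failure to the earliest treatment failure. On this view, success at a visit is shorthand for the status just defined, and an empty rebound row shows that the literal reading was never meant.

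This stands as evidence of intent. It identifies the visit-level sentence as the one to correct. It does not remove the contradiction, because that sentence is the only visit-by-visit classification rule in the protocol and it omits the condition. The lenient reading also fails on the fourth history above.

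Two limits on reach also stand:

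- The primary outcome measure in section 2.4 is time from randomization to virologic failure, with its own viral-load thresholds. The visit-level sentence does not alter it, and rebounds meeting those thresholds remain events.
- Table 2 is a 48-week display, whereas the primary objective is at week 24. The sentence applies to any visit, so week 24 is covered. However, a rebound with both values in by week 24 needs suppression by weeks 4 and 8, so fewer rebounds are exposed there. Early discontinuations remain exposed.

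**Conclusion.** The sentence is wrong as written and should be corrected before analysis. It conflicts with the responder definition in sections 2.6 and 3.4 and with the rebound and discontinuation rows of Table 2. Followed literally, it overstates tabulated response. At 85% true response the illustrative range is about 89% to 96% for f between 25% and 75%. A true 15-point gap would then appear as 11.25 to 3.75 points if f is the same in both arms. All of these figures rest on assumed values of f and on the literal reading.

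A reader might infer more: that the protocol adopts an ever-suppressed endpoint, that loss of response can no longer be counted, or that a bias toward comparability has been shown. The documents do not support these readings. Maintenance was evidently intended, the section 2.4 outcome still counts virologic rebounds, and nothing in the protocol fixes how failures divide before and after suppression, or between arms. The finding concerns the responder classification and Table 2, not every efficacy measure.

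**What to change.** Replace the visit-level sentence in section 3.4 and the one after it. Suggested text:

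> A subject is a success at a visit only if two consecutive viral loads below 50 copies/mL have been achieved and, since then and up to that visit, there has been no replicated rebound (two consecutive values of 50 copies/mL or more, dated to the first of the two) and no discontinuation or change of the randomised regimen. Subjects who died or were lost to follow-up by that visit are placed in the corresponding rows of Table 2. All others are classified by the reason for the earliest failure.

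The dating clause matters. Without it, a subject with values of 50 or more at weeks 24 and 32 would still be a success at week 24, because only one of the two values exists by then. The responder definition does not name death or loss to follow-up. They are included here because Table 2 has rows for them.

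The cost is a short rewording with no new data or visits. Reported response may be a few points lower than under the present sentence.
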